### Statistical methods: Analysis to handle protocol non‑adherence and any statistical methods to handle missing data

After the initial data collection, mechanical ventilator-free days on the 28th day, and brain dysfunction will be recorded. Patients will be included if there is missing data. In the event of missing data, imputation will be performed by calculating the mean of the available data. Patients will be excluded from the study if the quality of the TCD recording is deemed unsatisfactory.

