### Study outcome

The primary endpoint is to assess the impact of different MAP targets on cerebral hemodynamics (ARI, CrCP, RAP by TCD, and P2/P1 by B4C) in patients with septic shock.

Secondary objectives: (1) Evaluate the effects of targeting a MAP of 65 mmHg on cerebral hemodynamics in patients with septic shock. (2) Evaluate the correlation between ARI and B4C. (3) Correlate criteria of clinical severity and neurological dysfunction with cerebral hemodynamics (This will involve assessing the correlation between markers of organ dysfunction such as lactate levels, usage of vasoactive drugs, Sequential Organ Failure Assessment (SOFA) score, and delirium with CA). (4) Assess 28-day mortality.

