## Methods: Data collection and management

Data collection on admission will include the following: demographic characteristics, comorbidities, source of infection, Sequential Organ Failure Assessment at ICU admission, temperature, hemogram lactate, hepatic and renal markers, Glasgow Coma scale or Richmond Agitation Sedation Scale, Confusion Assessment Method for the ICU scale, drug for sedation, neuromuscular blocking agents, mechanical ventilation, quantify vasoactive drug dose on collection day, arterial blood gasses before and after the protocol, presence of acute cardiac dysfunction by echocardiography and left ventricle ejection fraction. We will describe the utilization of antipsychotics or sleep-improving medications before ICU admission.

At the time of data collection, the presence of brain dysfunction associated with sepsis will be assessed by: a Glasgow scale score < 15 or when disorientation, disorganized thinking, or agitation are reported by the attending physician, regardless of sedative/analgesic use and in the absence of neurological disease (i.e., dementia, cerebrovascular disease, brain tumors, previous traumatic brain injury). Data from medical records will be used to access such information, the description of the change in the level of consciousness or the use of antipsychotics or dexmedetomidine will be interpreted as a brain dysfunction.

Systemic physiological monitoring will be performed by an arterial line, cardioscopy, pulse oximetry, and capnography (if unavailable at the time of collection, this will be described). Before starting the monitoring, the proper functioning of the arterial line will be confirmed and the site described.

Each patient will adhere to a uniform protocol where, after establishing baseline measures, the mean arterial pressure (MAP) targets will be sequentially increased in the order of 65, 75, and then 85 mmHg. This structured approach ensures sample homogeneity.

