CA assessment by TCD will use a 2 MHz probe, supported by a helmet frame, the middle cerebral artery will be located through the window of the temporal bone, then it will be confirmed by depth and waveform, and one of the sides will be chosen and will be kept during the protocol. All hemodynamic parameters will be collected simultaneously and transmitted to the Doppler Box through a cable connected to the multiparameter monitor. A B4C sensor will be placed on the contralateral temporal window, which consists of a monitor that quantifies local cranial bone deformations using strain-gauge sensors. The system will be positioned on the frontotemporal region, approximately 3 cm over the first third of the orbitomeatal line, and the software will indicate the wave quality generated. The measurement of ICC will be done using the curve generated by B4C, and P2/P1 > 1 will be considered altered. The quality of measurements will be closely monitored during the duration of recordings to ascertain their acceptability for subsequent stages of off-line analysis.

The instantaneous relationship between arterial blood pressure and CBv will be used to estimate CrCP and RAP for each cardiac cycle using the first harmonic method [18]. Beat-to-beat data will be spline interpolated and resampled at 5 Hz to produce signals with a uniform time base.

Dynamic CA will be assessed using transfer function analysis, using spontaneous fluctuations of MAP as input and corresponding changes in CBv as output in recordings for each MAP target (lasting 5 min), as described previously [19,20]. The Welch method will be adopted for smoothing spectral estimates obtained with the fast Fourier transform (102.4 s segments, 50% superposition) leading to frequency-dependent estimates of coherence, gain and phase. Using the inverse fast Fourier transform, the CBv response to a step change in MAP will also be derived and compared with ten template curves proposed by Tiecks et al. [21] to estimate the ARI [22,23] Baseline cerebral hemodynamic parameters will be reported as the average over a 5-min recording at rest. Values of ARI < 4 will characterize impaired dCA.

The protocol will be interrupted if at any time during the data collection any of the adverse effects, described below, are identified.

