## Statistical methods: Outcomes

Data will be assessed for normality using the Kolmogorov–Smirnov test. Categorical variables will be compared using the Fisher exact test or chi-square test, as appropriate, and the Student t-test or the Mann–Whitney U-test will be used to compare continuous variables, as appropriate The results will be expressed as the average and standard deviation for normally distributed data, or as the median and interquartile ranges (IQRs) for non-normally distributed data.

The primary outcome will be evaluated at T0 (basal), T1 (65 mmHg), T2 (75 mmHg), and T3 (85 mmHg) using a two-way repeated-measures ANOVA. Due to the longitudinal study design and the dependence between repeated measures, mixed-effects regression models will be considered to develop a model with different pressure targets. Each component of cerebral hemodynamics (ARI, RAP, CrCP, and P1/P2) will be assessed individually. At the 65 mmHg MAP target, cerebral hemodynamics will be evaluated by mean and IQRs.

All secondary outcomes will be exploratory and analyzed using independent samples t-tests, and chi-square test, as appropriate, without additional adjustment. Linear regression, Pearson’s correlation coefficient or Sperman coefficient will be used to test for association between cerebral parameters and organ dysfunction. Statistical analyses will be performed using the last version of SPSS for Windows (Chicago, USA). A p-value<0.05 will be considered statistically significant.

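### Unrestricted single mean imputation distorts the primary comparison across MAP targets, and excluding whole patients for poor TCD discards valid data

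*Protocol article*

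**What the plan says.** The section on protocol non-adherence and missing data in the protocol article sets three rules:

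- Incomplete patients stay in: "Patients will be included if there is missing data".
- Gaps are filled: "In the event of missing data, imputation will be performed by calculating the mean of the available data".
- Poor Doppler removes the patient: "Patients will be excluded from the study if the quality of the TCD recording is deemed unsatisfactory".

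The sentence just before these rules concerns ventilator-free days and brain dysfunction, but the imputation rule is not limited to those items.

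Under Data collection and management, the MAP "targets will be sequentially increased in the order of 65, 75, and then 85 mmHg", and "The protocol will be interrupted if at any time during the data collection any of the adverse effects, described below, are identified".

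Under Statistical methods: Outcomes, the primary outcome is evaluated at T0 to T3 "using a two-way repeated-measures ANOVA", each parameter on its own. The same paragraph adds that "mixed-effects regression models will be considered to develop a model with different pressure targets". The primary endpoint (Study outcome) combines three TCD parameters (ARI, CrCP, RAP) with P2/P1, which comes from the separate B4C sensor.

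**The concern.** Single mean imputation treats a filled-in value as if it had been measured. The analysis then counts more observations than exist and ignores what the patient's other recordings say about the missing one.

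Repeated-measures ANOVA needs a complete row per patient, so the imputed values go straight into the primary test. The design also suggests where gaps will fall. Targets rise in a fixed order and the session stops on an adverse effect, so an early stop removes the later targets, mainly 85 mmHg, for a reason that may be tied to the patient's condition.

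The rule also does not suit every variable it covers. Brain dysfunction is defined as present or absent, and a mean is not a possible value for it.

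The exclusion rule raises a different issue. A patient with unusable Doppler may still have good P2/P1 recordings, good Doppler at other targets, and follow-up. Removal after enrolment, with no stated threshold, loses these and changes who is analysed.

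The results are also meant to inform sample sizes for later studies (Sample size section), so distorted estimates and variances would be carried forward.

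**Working it through.** **Inputs from the article.** At least 40 patients (Study setting); four conditions T0-T3; p < 0.05, taken as two-sided. It gives no missing-data rate, SD, correlation or effect size, so there is no planned figure to reproduce.

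**Assumptions.** n = 40, SD 1 at each condition, equal within-patient correlation ρ of 0.5 or 0.7, and a fraction f = 10, 20 or 30% missing T3. Means are 0 at T0 and T1, 0.25 at T2 and 0.50 at T3, or no change for the type I error. Simulations used 8,000 runs per scenario.

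**1. Across-patient mean, lost completely at random**

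- Reported variance of T3-T1: [2 - f - 2ρ(1-f)]/n
- True variance: [1/(1-f) + 1 - 2ρ]/n
- The first is (1-f) times the second, so the SE ratio is sqrt(1-f) for any ρ.
- At f = 0.2, ρ = 0.7: reported sqrt(0.68/40) = 0.130; true sqrt(0.85/40) = 0.146; ratio 0.89.
- At f = 0.1 and 0.3 the ratios are 0.95 and 0.84.
- Simulation at f = 0.2, ρ = 0.7: 95% interval coverage 92.0%; ANOVA type I error 7.9%.

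The T3 mean taken alone is affected more. Its SD ratio is sqrt(31/39) = 0.89 and its SE ratio 0.89 × sqrt(32/40) = 0.80. That is not the primary contrast.

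Variances passed to later studies are also wrong, in either direction. The T3 variance is 31/39 = 0.79 of the true one. The variance of the T3-T1 difference becomes 0.68 against a true 2(1 - 0.7) = 0.60.

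**2. Across-patient mean, T3 lost more often in patients with low T2 values (simulation)**

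| Missing | Bias in T3-T1, ρ = 0.5 to 0.7 |
|---|---|
| 10% | +0.08 to +0.11 SD |
| 20% | +0.14 to +0.20 SD |
| 30% | +0.20 to +0.28 SD |

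At 20% and ρ = 0.7, coverage is 72.7% and type I error with no effect is 28.1%. The SE is nearly right here (ratio 0.97 to 0.98), so bias is the problem.

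**3. Patient's own mean**

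- Lost completely at random, the expected contrast is (1-f) × 0.50 + f × (0.25/3): 0.458, 0.417 and 0.375 at 10, 20 and 30%. Simulation gives 0.456, 0.415 and 0.376.
- With T2-dependent loss it is 0.33 to 0.45.
- At 20%, ρ = 0.7, the reported SE is 0.116. With nothing missing it would be sqrt(0.60/40) = 0.122. Losing data therefore appears to improve precision.
- That SE does match the spread of the shrunken estimate (ratio 1.01). Coverage is 89.1% because the estimate is biased. With no true effect, type I error stays at 5.0%.

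**4. No imputation, using T0-T2 as a likelihood-based model would**

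Bias is within 0.003 SD throughout. The empirical SD at 20%, ρ = 0.7 is 0.134 (completely at random) to 0.141 (T2-dependent), against reported SEs of 0.130 to 0.139 (across-patient mean) and 0.116 to 0.118 (own mean).

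**5. Excluding incomplete patients**

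The complete-case SE of T3-T1 is correctly calibrated (ratio 0.97 to 1.00).

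**The case against.** The case on the other side has real force.

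- **Non-random loss is not shown.** The adverse effects listed in the harms section are arrhythmia and intestinal or extremity ischemia, not a hemodynamic index, and derived parameters are not available during recording. Patients unstable from acute arrhythmia or at imminent risk of death are excluded, so stops may be few. This stands against any firm error rate from the T2-dependent scenario. A reader might take 28.1% as a forecast; it is only what that assumed mechanism would produce.
- **The direction is open.** A reader might infer that the rule makes higher MAP look better. That needs the across-patient mean and a particular stopping pattern, and it depends on the parameter: for P2/P1 a higher value is worse. The own mean pulls the contrast towards zero.
- **Exclusion does not shrink the standard errors.** Only imputation does so. The objection to exclusion is selection and lost data.
- **The rules need not contradict each other.** Keeping incomplete patients and removing those with unusable Doppler can coexist, and the recording may mean the whole session. Signal quality is monitored during recording, before derived values exist, so part of the safeguard is in place. No threshold is stated.
- **Correlations at 65 mmHg.** Loss of T3 does not weaken them; 65 mmHg is the first target and the least exposed to early stops.
- **Deaths.** The article does not say that values after death count as missing, so imputing them is only an inference.
- **Follow-up only.** The rule may have been meant for follow-up items. The text does not say so, and a mean would still not suit brain dysfunction.
- **It is a pilot that already names mixed models.** True, but these are only to be considered, and the ANOVA is the stated primary analysis.

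**Conclusion.** The concern holds: an unrestricted rule of single mean imputation is wrong as written for the primary comparison. With the across-patient mean and loss completely at random, the SE of the affected contrast is too small by the factor sqrt(1-f), whatever the correlation, and type I error is about 8% at 20% missing. Bias is added if stopping relates to the patient's state, which the ascending order and the interruption rule make plausible but do not establish. With the patient's own mean, a real difference is diluted and its SE is reported as smaller than complete data would give, although the test keeps its level when there is no effect.

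The actual size and direction cannot be determined from the article. If few recordings are lost, the harm is small. Whole-patient exclusion for poor TCD is a separate and lesser defect: lost P2/P1, other targets and follow-up, and selection after enrolment without a stated criterion.

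**What to change.** - Delete the mean-imputation sentence.
- Make the mixed-effects model already named the primary analysis for each parameter: REML, a patient random effect, MAP condition as a factor, all usable recordings, no imputation.
- Report the number of recordings per target and the reason for each missing one. The model still assumes that loss is explained by the recorded data, so a sensitivity analysis for sessions stopped on an adverse effect is a useful addition.
- Replace the exclusion rule: reject an unusable TCD recording for ARI, CrCP and RAP only, by a signal-quality criterion fixed in advance. Keep that patient's P2/P1, other targets and follow-up.
- Do not fill in brain dysfunction with a mean; report it as observed, with denominators.

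The cost is a change of wording. No extra measurement is needed, and SPSS, the planned software, fits the model. Precision will be stated slightly less favourably.

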#### Selection criteria

Study enrollment will include patients experiencing septic shock for up to 48 hours and still necessitating vasopressor support. Detailed inclusion and exclusion criteria are provided in Table 1.

**Table 1 pone.0304412.t001:** Selection criteria.

Inclusion criteria	Exclusion criteria
• Age > 18	• No temporal window for TCD
• Septic shock < 48h • The timing will be counted from ICU admission or the start of noradrenaline infusion for patients already in critical care units.	• Hepatic or uremic encephalopathy
	• Pregnancy
	• Acute or prior neurological insult*
	• Exogenous intoxication
	• Dementia**
	• Severe hypercapnia*** • Instability for acute arrhythmia
	• Extracorporeal support device by modifying the pulse waveform****
	• Extreme severity, with imminent risk of death

* Ischemic or hemorrhagic stroke, aneurysm, arteriovenous malformation, hydrocephalus, neurological surgery, central nervous system infection.

** Reported or written in medical records.

*** Partial pressure of arterial carbon dioxide (PaCO2) > 65mmHg.

**** Intra-aortic balloon pump (IABP) and Extracorporeal membrane oxygenation (ECMO).

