#### Adverse event reporting and harms

Serious adverse events (SAEs) encompass various potential outcomes, including arrhythmia, intestinal ischemia, and acute extremity ischemia. These events tend to occur more frequently when administering exceedingly high doses of vasopressors, particularly among patients with an imminent prognosis of death within a few hours or those already exhibiting arrhythmias. Consequently, such cases are excluded from the study. Given the anticipated higher mortality rates within this patient cohort, instances of death are not reported as SAEs in this context.

Furthermore, each type of SAE and the total number of SAEs will be reported in the REDCap database and do not have to be reported separately.

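### A patient can be removed from the whole study for a poor TCD recording after the pressure steps have begun, and the protocol does not say that such patients stay in the harm summary

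*Protocol article*

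**What the plan says.** All places are in the protocol article.

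- **Exclusion for quality** (Statistical methods, non-adherence and missing data): "Patients will be excluded from the study if the quality of the TCD recording is deemed unsatisfactory". No threshold, timing or assessor is given.
- **Missing data** (same paragraph): "Patients will be included if there is missing data".
- **When quality is judged** (Data collection and management): "The quality of measurements will be closely monitored during the duration of recordings to ascertain their acceptability for subsequent stages of off-line analysis".
- **Entry screen** (Table 1): "No temporal window for TCD" is an exclusion criterion.
- **Exposure** (Data collection and management): after baseline, "the mean arterial pressure (MAP) targets will be sequentially increased in the order of 65, 75, and then 85 mmHg".
- **Interruption** (same section): "The protocol will be interrupted if at any time during the data collection any of the adverse effects, described below, are identified".
- **Harms** (Adverse event reporting and harms): "each type of SAE and the total number of SAEs will be reported in the REDCap database". The types named are arrhythmia, intestinal ischemia and acute extremity ischemia. The Interim analysis section adds that adverse effects go to the Ethics Committee.

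The article defines no safety population and no denominator for harms.

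**The concern.** The quality rule acts on the patient and on the study, although the defect it addresses affects only the TCD-derived measures. Three of the four primary components (ARI, CrCP, RAP) come from TCD. The fourth, P2/P1, comes from the B4C sensor on the other side of the head and may be sound when the TCD signal is not. Brain dysfunction on days 7 and 28, ventilator-free days and 28-day mortality do not depend on TCD at all.

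The rule can also operate after exposure, for a reason that is not independent of harm. An adverse effect stops the session, a stopped session may leave a short or degraded recording, and such a recording may be deemed unsatisfactory. If the patient then leaves the study, the text does not say whether that patient's event, and that patient's place in the denominator, stay in the harm summary.

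The study is a pilot meant to inform later ones. How well the MAP steps are tolerated, and how often a session fails, are results those studies would want from it.

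**Working it through.** The article gives no harm rate, exclusion rate or sample-size calculation, so there is no planned figure to reproduce. The only document inputs are the target of at least 40 patients, the 5-minute recording per target and the Welch settings ("102.4 s segments, 50% superposition"). Every rate below is an assumption.

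**Step 1: can exclusion follow exposure?** Table 1 removes only patients without a temporal window. A signal that fails later is found during the recordings or off-line, and the recordings at 65, 75 and 85 mmHg are made while the steps are under way. So it can. A poor baseline signal could also lead to exclusion before any step.

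**Step 2: can an interruption spoil a recording?** The number of Welch segments in L seconds is floor((L − 102.4)/51.2) + 1 if L ≥ 102.4, and 0 otherwise.

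- L = 300: (300 − 102.4)/51.2 = 3.86, so 3 + 1 = 4 segments.
- L = 153: (153 − 102.4)/51.2 = 0.99, so 0 + 1 = 1 segment.
- L = 102: no segment.

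An early stop can leave the current step with one segment or none for the ARI. Steps completed earlier remain usable.

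**Step 3: what could this do to a harm rate?** Let p be the true proportion harmed among those exposed, e1 the probability of exclusion if harmed, and e0 the probability if not.

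- A, excluded patients leave numerator and denominator: p(1 − e1) / [p(1 − e1) + (1 − p)(1 − e0)]
- B, all events kept but only analysed patients in the denominator: p / [p(1 − e1) + (1 − p)(1 − e0)]
- C, all exposed patients in both: p

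With p = 10%:

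| e1 | e0 | A | B | C |
|---|---|---|---|---|
| 10% | 10% | 10.0% | 11.1% | 10.0% |
| 30% | 10% | 8.0% | 11.4% | 10.0% |
| 50% | 10% | 5.8% | 11.6% | 10.0% |
| 80% | 10% | 2.4% | 12.0% | 10.0% |
| 10% | 20% | 11.1% | 12.3% | 10.0% |

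For example, with e1 = 50% and e0 = 10%: A = 0.05/(0.05 + 0.81) = 5.8% and B = 0.10/0.86 = 11.6%.

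**Step 4: the same in counts.** Assume 40 exposed and 4 harmed, with 3 of the 4 harmed and 3 of the 36 others excluded, which leaves 34.

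- C: 4/40 = 10.0% (exact 95% CI 2.8 to 23.7%)
- A: 1/34 = 2.9% (0.1 to 15.3%)
- B: 4/34 = 11.8% (3.3 to 27.5%)

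A falls below the true rate only when e1 exceeds e0. It equals the true rate when the two are the same and exceeds it when e1 is lower. B is above the true rate whenever anyone is excluded. C does not depend on either.

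**The case against.** A reader might infer that the protocol will under-report harm. The documents do not support that.

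- No sentence drops the events of excluded patients. SAEs are to be entered by type and in total, adverse effects go to the Ethics Committee, and SAE reports are covered by monitoring. None of this is tied to TCD quality. **This stands**, and it is why a downward bias cannot be asserted.
- No harm rate is planned, only counts, so the denominator has to be supplied by the reader. **This stands** as a limit on the claim. But counts need a stated number exposed to be read, and the quality rule makes that number unclear.
- A stopped session first of all leaves later MAP levels missing, and patients with missing data stay in. **This stands in part.** The article does not say whether a truncated recording is missing or unsatisfactory, and the two rules lead to opposite results.
- It is also tempting to say that sessions stopped for harm are the ones most likely to give unusable TCD. No figure supports that. Of the named SAEs, arrhythmia has the most evident route to a degraded signal, and Table 1 already excludes instability from acute arrhythmia. **This stands:** the link is plausible, not documented.
- The sentence sits under missing-data methods and may have been meant as an exclusion from analysis, and an article may leave a safety population to a fuller document. **This does not remove the point.** The objection here is to a stated rule whose wording reaches the whole study, not to something left out.

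**Conclusion.** The point holds in conditional form. The quality rule, as written, allows exposed patients to be removed from the study for a TCD-only fault, at a time and for a reason that may be related to harm. The literal consequence is loss of their B4C data and follow-up. The possible consequence is a biased harm summary, whose direction the article does not settle: downward if excluded patients' events leave with them and harmed patients are excluded more often than others, upward if all events are set against analysed patients only.

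In the assumed 40-patient example, a true 10.0% would be shown as 2.9% or 11.8%. The confidence intervals overlap widely, and the example shows sensitivity, not an expected size. Bias is possible and has not been shown. The wording is still worth correcting, because one sentence removes the dependence on both exclusion probabilities.

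**What to change.** Reword the sentence in the missing-data section so that:

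1. an unsatisfactory TCD recording is left out of the TCD-derived analyses (ARI, CrCP, RAP) only, with B4C and follow-up data retained;
2. every patient in whom a MAP change was started stays in the study and in both the numerator and the denominator for harms;
3. a recording cut short by an interruption is classed explicitly, as either missing or unsatisfactory.

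Report, at each MAP target, the numbers exposed, interrupted and with unusable TCD, and how many of the unusable recordings followed an interruption.

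The cost is a short rewording in the protocol or SAP and a row in the flow diagram. No new data are needed, and no rule on treatment or on stopping a session changes.
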